## Results

This study was approved and funded by the Brazilian Ministry of Health in October 2018 and was approved by the institutional review board in October 2019. Data collection started in January 2019 and is expected to finish in 2022. At the time of manuscript submission, 18 participants were recruited.

The primary objective of this study is to confirm the noninferiority of remote consultation in comparison with face-to-face consultation assessed by the change from baseline in HbA_1c_ (%) at 6 months. The noninferiority margin was set at 0.5%. Assuming an SD of 1.3% for both groups, true difference between the means of zero, and a type I error level of 5% (one-sided), it was estimated that 117 individuals per group would be necessary to achieve 90% power [30]. In order to accommodate for a maximum dropout rate of 5%, the sample size was increased to 124 individuals per group. Sample size calculation was performed using SAS version 9.4 (SAS Institute Inc, Cary, NC).

The primary endpoint in this study is the change from baseline in HbA_1c_ (%) at 6 months. The assessment of noninferiority of remote consultation in relation to face-to-face will be conducted according to the CONSORT guidelines [31], using the confidence interval approach to the difference in the mean of the primary variable between the 2 groups. If the upper limit of the 90% bilateral CI is lower than the established noninferiority margin (0.5%), the noninferiority of the remote consultation group relative to the face-to-face group is declared at the 5% significance level. In addition, an analysis of covariance (ANCOVA) model will be constructed using the main effects of treatment and baseline HbA_1c_ as the covariate.

Adjusted means by treatment will be presented as well as an estimate of the difference between adjusted means. A 90% 2-sided CI, based on the ANCOVA model, will be computed for the difference between adjusted means. If the upper limit of the 90% bilateral CI is lower than the established noninferiority margin (0.5%), the noninferiority of the remote consultation group relative to the face-to-face group is declared at the 5% significance level [32-34]. The primary endpoint will be analyzed for the intention-to-treat (ITT) and per-protocol populations. If the proportion of missing data is greater than 5%, sensitivity analyses for missing data imputation will be performed [35,36].

The secondary endpoint is the change from baseline in HbA_1c_ at 3 months, which will be evaluated with ANCOVA. Adjusted means (with 95% CI) by treatment will be presented. Mixed effects, repeated measures models will be considered for secondary endpoints defined by continuous variables over time (baseline, 3 months, 6 months). Comparison of secondary endpoints defined by categorical data will be evaluated using chi-square or Fisher exact tests. Secondary endpoints will be performed as 2-sided tests with an alpha of 5%, and 95% CIs will be reported. The proportion of adverse events will be compared between the 2 groups via a Fisher exact test. The secondary endpoints will be analyzed on the ITT population.

Baseline characteristics will be compared and summarized by treatment groups for the ITT population. Categorical data will be summarized by numbers and percentages. Continuous data will be summarized by mean, SD, and range if data are normal and median and IQR if data are skewed. Normality will be assessed by visual inspection of histograms and with the Shapiro-Wilk normality test [36]. Baseline variables will be compared with the chi-square test or Fisher exact test for categorical variables and the *t* test or Mann-Whitney test for continuous variables. Statistical analyses will be performed using SAS version 9.4.

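### Missing-data sensitivity analyses are triggered only above the planned maximum dropout of 5%, and the stated primary analyses leave out the 3-month HbA1c

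*Protocol article*

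**What the plan says.** All of this is in the Results section of the protocol article unless noted.

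- The missing-data rule for the primary endpoint is: "If the proportion of missing data is greater than 5%, sensitivity analyses for missing data imputation will be performed".
- The sample size paragraph uses the same percentage: "In order to accommodate for a maximum dropout rate of 5%, the sample size was increased to 124 individuals per group".
- The primary endpoint, change in HbA1c at 6 months, is assessed by a 90% two-sided confidence interval for the mean difference. An ANCOVA with treatment and baseline HbA1c is added. Noninferiority is declared if the upper limit lies below 0.5. Both the ITT and the per-protocol populations are analysed.
- HbA1c is also measured at 3 months (Methods), where it is a secondary endpoint with its own ANCOVA. Models that combine visits are mentioned only for the secondary endpoints: "Mixed effects, repeated measures models will be considered for secondary endpoints defined by continuous variables over time (baseline, 3 months, 6 months".

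The article does not say how a missing 6-month value is handled in the ITT analysis, nor whether the 5% is counted overall or per arm.

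**The concern.** Because the trigger equals the dropout allowance, the robustness check is switched off in the situation the trial was designed for. A percentage missing also says nothing about which patients are missing or from which arm.

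The trial is open-label, so a patient who does badly on remote consultation knows which arm he or she is in and may leave. Losing poor responders from the remote arm makes its mean look better, and in a noninferiority trial that error favours the claim. The per-protocol analysis gives no protection, because it lacks the same outcomes. The 3-month HbA1c is the best information available on patients who leave between months 3 and 6, yet neither stated primary analysis uses it.

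**Working it through.** **Inputs from the article (Results).** "The noninferiority margin was set at 0.5" (HbA1c percentage points). "Assuming an SD of 1.3% for both groups". "true difference between the means of zero". One-sided alpha is 5%. "117 individuals per group would be necessary to achieve 90% power". Enrolment is 124 per group, or 248 in all.

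**The plan's own figure.** n = 2 × 1.3² × (1.645 + 1.282)² / 0.5² gives 116 per group by the normal approximation. The noncentral t calculation gives 117 (power 0.901; 116 gives 0.899). Then 117 / 0.95 = 123.2, rounded up to 124. The stated sizes reproduce.

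**What escapes the trigger.** 0.05 × 248 = 12.4, so 12 missing outcomes overall prompt nothing. Counted per arm, 0.05 × 124 = 6.2, so 6 in each arm escape on either reading.

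**Simple bound.** Assume remote dropouts end d points worse than remote completers, while face-to-face dropouts resemble completers. Then:

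- bias = d × (missing in remote arm) / 124
- SE = 1.3 × √(1/n_remote + 1/n_face-to-face), using completers
- type I error at a true difference of 0.5 = Φ(−1.645 + bias/SE)

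Example with 6 missing per arm and d = 1: bias = 6/124 = 0.048; SE = 1.3 × √(2/118) = 0.169; Φ(−1.645 + 0.286) = 0.087.

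| Missing, remote / face-to-face | d = 0.5 | d = 1 | d = 2 |
|---|---|---|---|
| 6 / 6 | 6.7% | 8.7% | 14.2% |
| 12 / 0 | 8.7% | 14.1% | 30.8% |

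The values of d are assumptions; the article gives none.

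**Simulation.** The set-up was 124 per arm, SD 1.3, a true difference of 0.5 at both visits, and 8,000 trials per scenario. Remote dropout odds rise with a worse 3-month change (log-odds 1.5 per SD), and face-to-face dropout is random. Baseline is omitted for simplicity. The two figures in each cell are for 3-/6-month correlations of 0.5 and 0.7.

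| Dropout, remote / face-to-face | Completers' estimate | Completers' type I error | Type I error, likelihood estimate using 3-month value |
|---|---|---|---|
| 5% / 5% | 0.46, 0.44 | 8.3%, 10.4% | 5.0%, 5.0% |
| 10% / 0% | 0.42, 0.38 | 11.7%, 17.6% | 4.6%, 5.2% |

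Varying the log-odds from 1 to 2 widens the completers' ranges to about 7–12% and 10–19%. If the same selection acts in both arms, dropout of 7% remote and 3% face-to-face gives about 7–9%. Dropout of 5% in each arm then gives no inflation.

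**Near the planning assumption.** With an observed difference of 0 and 6 remote outcomes missing, the upper limit is 0.275, which leaves 0.225 to the margin. Overturning the result needs d = 0.225 × 124/6 = 4.65 points. With 12 remote outcomes missing, the slack is 0.221 and d = 0.221 × 124/12 = 2.3 points.

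**The case against.** Several objections have force.

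- **Completers only.** The article never says that the ITT analysis drops patients without a 6-month value. An analysis plan that is not shown may settle this. It is an inference, drawn because imputation is named only as a sensitivity analysis and no other method is given. The trigger and the ANCOVA terms, however, are stated rules rather than omitted detail.
- **Overall or per arm.** The 10%/0% case escapes the trigger only if 5% is counted overall. The 6/6 case escapes either way.
- **Unchecked bias.** A reader might infer that selective dropout in general can produce false noninferiority unchecked. The article does not support this: above 5% missing, where the bias can be largest, it commits to sensitivity analyses.
- **Asymmetry.** Endocrinologists, consultation length and consultation protocol are the same in both arms (Methods), and equal, equally selective dropout causes no inflation. This stands. The concern needs dropout that is more common or more selective in the remote arm, which an open-label design makes possible but the article does not establish.
- **A partial check exists.** The 3-month ANCOVA in the ITT population includes patients who leave after month 3. It carries no noninferiority rule, so it helps but does not close the gap.
- **The comparison flatters the alternative.** The likelihood estimate stays unbiased in the simulation because dropout there depends on the observed 3-month value. If dropout depends on unobserved later values, that model alone is not enough.

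Nor is the baseline-adjusted ANCOVA an error in itself. It is a standard analysis for a single time point.

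**Conclusion.** The point holds in limited form, as a should-fix. The trigger coincides with the planned maximum dropout, so a trial that runs to plan gets no missing-data sensitivity analysis, and the stated primary analyses ignore relevant data already in hand.

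The inflation to about 7–12%, or about 10–19% with all dropout in the remote arm, rests on four assumptions: a true difference at the margin, a completers' primary analysis, selection on the 3-month result with log-odds of 1 to 2 per SD, and 3-/6-month correlations of 0.5 to 0.7. None of these is a figure from the article. If the true difference is near zero, as the sample size assumes, the noninferiority conclusion is hard to overturn at this level of missingness.

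**What to change.** 1. Delete the 5% trigger, so that missing-data sensitivity analyses are run whatever the proportion missing.
2. Estimate the 6-month contrast from a repeated-measures model of HbA1c at 3 and 6 months in all randomized participants, with arm-by-visit and baseline-by-visit terms and an unstructured covariance. With complete data this gives the ANCOVA estimate; without the baseline-by-visit term it need not. The minimum alternative is to keep the ANCOVA and put the 3-month HbA1c in the imputation model.
3. Always report a tipping-point analysis that makes missing remote-arm values progressively worse until noninferiority is lost. This covers dropout that the 3-month value does not explain.

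The cost is analysis wording and a little more SAS programming. The 3-month HbA1c is already collected, and the sample size does not change. With 18 participants recruited at submission, the change could be made before outcomes are known.

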## Discussion

Brazil is a country of continental proportions, with great heterogeneities and gaps in access to health care, types of health services, and specialized medical professionals. Lack of access to health services is one of the main indicators of social inequality in Brazil. Thus, to improve access, there is a need to build strategies that impact primary health care, the processes that regulate access, and the organization of specialist care. In this context, studies have shown telemedicine to be equivalent to face-to-face care, and it can be an effective solution to increasing patient access to services, especially to specialist doctors.

Providing evidence of the efficacy and safety of remote treatment for different conditions in Brazil will contribute to improving patients’ access to the public health system, including specialist doctors. This evidence can also help to remove restrictions placed on remote consultation by the Brazilian Federal Medicine Council, which currently restricts direct specialist-to-patient consultation. This model of improved access can help to meet the health needs of the population, breaking the geographical barriers that a country like Brazil imposes on the provision of health services. In addition to greater access to health care, the use of telemedicine has potential economic benefits for health systems and can be used safely to deliver a quality service.

Our expectations are that providing remote access to health care will result in improvements in the health and quality of life of patients with type 2 diabetes and reduce costs and that both patients and clinicians will benefit from and be satisfied with this technology.

## Abbreviations

ANCOVA: analysis of covariance
HbA_1c_: glycated hemoglobin
ITT: intention-to-treat
SUS: Unified Health System (in Portuguese)
TDABC: time-driven activity-based costing
